### Sample Variables

2.9

Gender and age; Marital status; Educational qualification; Previous and current employment status; Past and current organic physical pathologies; Previous and current mental health diagnosis; Drugs in use.

### Data Analysis

2.10

The outcome of the trial was analyzed through multivariate analysis of variance (MANOVA). Through this procedure, the sample means of the dependent variables (scores in the performance tests) were compared in sub-samples divided by the two independent variables [time and group (intervention and non-intervention)]. For variables not on an interval scale, the analysis of variance for nominal data by De Castellan was used with a similar methodology.

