## INTRODUCTION

1

Bipolar disorder is a range of chronic diseases characterized by recurrent episodes of mania/hypomania, depression, and euthymia (mood dysregulation); dysregulation in sleep/wake rhythm, and medical and psychiatric comorbidities [1]. Community surveys found that the lifetime prevalence of Bipolar disorder ranges between 1% and 2.4%, although the methodology of published studies may underestimate its prevalence [2]. The disease is highly disabling due to its early onset, severity and chronicity: it is considered one of the leading causes of disabilities in the world [3], accounting for 7.0% of all DALY’s due to mental and substance use disorders [4-6]. Alongside effective symptoms, cognitive impairment is believed to be a core component of bipolar disorder [7], and in the long-term bipolar disorder was found to be associated with a high risk of dementia [8, 9]. Overall, approximately 40% to 60% of people that experienced one or more episodes of bipolar disorder have neurocognitive impairment [10]. Neurocognitive dysfunctions may be found in premorbid stages, before the disease onset [11], in the early course of the illness [12], and during the euthymia phase [13]. Poor cognitive performance impacts negatively on occupational and social functioning [14], increases the hospital admissions, affects direct/indirect healthcare related costs [15], hinders the benefits of psychotherapy [16], and represents a barrier to achieving adequate social and occupational functioning and a good quality of life [17]. The affected domains included attention, processing speed verbal learning/memory, memory, and executive functions including cognitive flexibility, inhibitory control, and working memory [18, 19]. Despite the growing attention paid to identifying and treating cognitive impairment in bipolar disorder, evidence is still lacking on effective interventions aiming to minimize cognitive symptoms in these patients [20]. Lithium was deemed to have an indirect positive effect on cognition in bipolar disorder, but other drugs used in the treatment of bipolar disorder entail cognitive side-effects related with extrapyramidal, sedative, anticholinergic, and blunting mechanisms [21]. The term Cognitive Remediation (CR) implies interventions based on behavioral training that aims to improve cognitive processes (memory, attention, executive functions, social cognition, and metacognition), which have to be exerted long enough to guarantee the persistence of the results and their generalization [22]. Different approaches were used, ranging from paper-and-pencil to computerized-based rehabilitation program to mixed interventions [23, 24]. Initial evidence suggests that CR and physical activity may exert protective effects for the prevention of cognitive decline [25], and CR has been found to be effective in the treatment of various psychosocial disorders (including bipolar disorder) to improve the cognitive and social-occupational domains, although the evidence base is still inconclusive [20, 26, 27]. Recently, Virtual reality (VR) emerged as a promising rehabilitation tool, with a growing number of studies suggesting that VR may facilitate learning and/or enhance different skills, thanks to the ability to make learning experiences real and ecological compared with traditional intervention techniques [28-30]. Current research on the clinical use of VR software has led to positive results, especially in cardiovascular, neurological, and musculoskeletal rehabilitation [31. 32]. In mental health, the evidence is limited to rehabilitation of social cognition in people with schizophrenia, and the psychotherapy of anxiety disorders and phobias, it is increasing the focus on the use of VR for CR interventions especially for schizophrenia and mild cognitive impairment [33]. To date, there are no studies in which VR was used as a CR intervention to improve the cognitive processes related with the personal and social functioning of people diagnosed with bipolar disorder. Given the ability of VR to facilitate and generalize the learning of the trained skill and its capacity to favor engagement in the task [30] and that CR may exert protective effects for the prevention of cognitive decline, therefore, it is important to promote randomized controlled clinical trials that evaluate the effectiveness of VR-implemented CR interventions. CEREBRUM is one of the first VR-implemented CR tools in the field of psychiatric rehabilitation in Europe, conceived, and designed by “PRoMIND - Services for mental health SRLS” (Rome) in association with “IDEGO - Virtual Psychology” (Rome).

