### Data collection

2.8

The data collection was made with a personal data sheet; consecutively the patients were enrolled at the Consultation and Psychosomatic Psychiatry Center of the University Hospital of Cagliari (San Giovanni di Dio Civil Hospital). The presence of possible side effects and satisfaction with the intervention was assessed through a self-report questionnaire, for the others, secondary outcome indicators were used, and a standardized evaluation tool validated in Italian and used in psycho-social research (in the case of a learning effect, different versions for retests were used). Participants were assessed before the treatment, after the end of the intervention, and after 6 and 12 months after the end of the intervention.

*For the cognitive evaluation was used:* Matrix test [38]; Rey Figure Test [39]; Rey's Words Test, in the two versions [40, 41]; Digital Symbol Substitution Test, in the two versions [42, 43]; Trail Making Test, in the two versions [44]; Normal and Inverse Digit Span, in the two versions [45, 46]; Stroop Test [47]; Frontal Assessment Battery - FAB [48]; Phonological and Semantic Verbal Fluency Test, in the two versions [41, 49]; Test of Cognitive Estimates (CET), in the two versions [50, 51]; Test of the Tale [52, 40].

*For the general evaluation was used:* SF-12, Short Form Health Survey with 12 items [53], a self-administering scale, which investigates the following dimensions of well-being: vitality, physical function, physical pain, perception of general health, mental health, physical and emotional, work functioning, and social role. TAS-20 Toronto Alexithymia Scale [54] self-administering scale, evaluates the level of emotional awareness. Self-Rating Scale (SAS) self-administered scale [55] evaluates perceived anxiety levels regardless of diagnosis. The Patient Health Questionnaire - PHQ-9, self-administering scale [56], evaluates depressive symptoms. Health of The Nation Outcome Scale - HoNOS [57] evaluates personal and social functioning and clinical performance. Biological Rhythms Interview of Assessment in Neuropsychiatry - BRIAN validated in Italian version [58], an interview consisting of 18 items that investigates 4 main areas related with the dysregulation of circadian rhythms (sleep, activity, social rhythms, and nutrition).

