## DISCUSSION

4

The primary aim of this trial is to study the feasibility (recruitment and retention rates to inform sample size calculations to confirmatory trials) of a VR-implemented CR tool (CEREBRUM), secondary to study cognitive and psychosocial variables. The hypothesis is that through a cognitive remediation virtual reality program, and using ecological instrument, it is possible to improve cognitive abilities and also the other social and personal outcomes. Their results were discussed with all the authors.

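### The MANOVA named for the test scores uses only complete outcome vectors, so one missing test discards other observed scores; how much is lost depends on a data layout that section 2.10 does not fix

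*Protocol article*

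**What the plan says.** Section 2.10 (Data Analysis) names the method: "The outcome of the trial was analyzed through multivariate analysis of variance (MANOVA"). It adds that "the sample means of the dependent variables (scores in the performance tests) were compared in sub-samples divided by the two independent variables", these being "time and group (intervention and non-intervention"). Variables that are not on an interval scale are handled separately: "For variables not on an interval scale, the analysis of variance for nominal data by De Castellan was used with a similar methodology".

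Section 2.8 (Data collection) lists 11 cognitive tests, beginning "Matrix test [38]; Rey Figure Test [39]; Rey's Words Test, in the two versions [40, 41"], and gives four assessment times: "Participants were assessed before the treatment, after the end of the intervention, and after 6 and 12 months after the end of the intervention". Section 2.11 gives 50 randomised participants.

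The design is a cross-over. Under section 2.3, group B starts CEREBRUM one month after group A has finished its three months, and group A then has routine care. The Conclusion justifies this design by the low variance obtained when each participant serves as their own control. Effectiveness is a secondary objective, described as preliminary (section 1.1.2). Completion of the intervention is a coprimary outcome (section 2.7).

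**The concern.** A MANOVA treats the dependent variables as one vector per record, and a record with any element missing is not used. The exclusion therefore follows from the method named, unless values are imputed first or tests are analysed separately. Eleven tests in 50 people give many chances for a gap, and each gap also removes scores that were observed.

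Two things are at stake. The first is precision in a small trial. The second, in one layout only, is selection. If a record spans all four visits, someone who took the end-of-intervention battery but missed month 12 drops out of the end-of-intervention comparison. That matters if people who do poorly are the ones who leave. The Introduction makes such a link plausible but does not establish it: it says poor cognitive performance "increases the hospital admissions, affects direct/indirect healthcare related costs [15], hinders the benefits of psychotherapy [16"], and says nothing about missed assessments. Retention is uncertain by the trial's own account, since it is one of the quantities the study sets out to measure.

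**Working it through.** **Inputs from the article:** 50 randomised (2.11); 11 cognitive tests and four assessment times (2.8); joint analysis of test scores by time and group (2.10). The sample size of 50 comes with no effect size, standard deviation or dropout rate, so there is no stated figure to reproduce.

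**Assumptions:** all 11 tests enter one MANOVA; each score is missing independently with probability m = 1% or 2% at an attended visit; dropout by month 12 is d = 10% to 30%. None of these is in the article. Tests that give several scores would make the losses larger. Tests that are not on an interval scale, or gaps that cluster in the same session, would make them smaller.

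**Layout 1: one row per visit.**
- Share of attended visits with all tests present: (1 − m)^11.
- m = 1%: 0.99^11 = 0.895, a loss of 10.5%. m = 2%: 0.98^11 = 0.801, a loss of 19.9%.
- Standard error relative to using every attended visit: 1/√0.895 = 1.06 and 1/√0.801 = 1.12, a rise of about 6-12%.
- A missed month-12 visit removes only that row. In a software check with 50 people and four visits, 15 missing month 12 left 185 of 200 rows and all 50 end-of-intervention rows. Blanking one score for 5 people at one visit cut the rows used from 200 to 195.
- In this layout, repeated visits by the same person count as independent records, which gives up the within-person advantage that the Conclusion claims for the cross-over.

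**Layout 2: one row per person over four visits.**
- Complete vectors: 50 × (1 − d) × (1 − m)^(11 × 4).

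| m | d = 0 | d = 10% | d = 30% |
|---|---|---|---|
| 1% | 32.1 | 28.9 | 22.5 |
| 2% | 20.6 | 18.5 | 14.4 |

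- Standard error relative to 50 participants: √(50/28.9) = 1.31 and √(50/14.4) = 1.86, a rise of about 31-86% across the dropout range.
- From a missed month 12 alone (m = 0), 10% or 30% absence discards 5 or 15 observed end-of-intervention records.

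**Bias, layout 2 only.** Simulation with 400,000 draws: pre-post correlation 0.7, true gain 0.3-0.5 SD, 20-30% lost after the end-of-intervention visit, odds of loss multiplied by 1.5-2 per SD worse. If loss depends on change, the estimated pre-post gain is too large by 12-49% of the true gain. If it depends on the post score, the excess is 5-19%. If loss is unrelated to outcome, the bias is about zero. These figures concern the pre-post gain, not the contrast between groups.

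**The case against.** The strongest objection is that section 2.10 is three sentences in a condensed article. It does not say that all tests enter one MANOVA, which times enter it, or that incomplete cases are deleted. Imputation beforehand would be compatible with the text. Missing-data rules and analysis sets are commonly left to a full protocol or analysis plan, so their absence here is no fault. This stands, and it is why the point concerns the method named and the size is conditional.

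A reader might infer that the plan restricts the effectiveness result to completers, or that a missed 12-month visit deletes end-of-intervention data. The document does not support that. It happens only with one row per person over all four visits, and the wording about sub-samples divided by time and group reads more naturally as one row per visit. The 31-86% and 5-49% figures belong to that one layout.

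A reader might also infer that a distorted effect estimate would feed into the confirmatory trial's sample size. The Discussion ties that to "recruitment and retention rates to inform sample size calculations to confirmatory trials", which MANOVA deletion cannot touch.

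The objection does not remove the core. Without imputation or separate analyses, either layout discards observed scores when one test is missing. The row-per-visit reading that avoids the worst loss also ignores the pairing within participants.

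**Conclusion.** The point holds in conditional form. The MANOVA as named loses observed data whenever a vector is incomplete. On the more literal layout the loss is moderate: about 10-20% of attended visits and a 6-12% rise in standard error, given 11 joint tests and 1-2% independent missingness. On the one-row-per-person layout it is severe, leaving 21-32 of 50 participants before dropout and 14-29 with 10-30% dropout; a tilt towards completers is then possible but needs outcome-related loss. All missingness and dropout rates are assumed. A better method is available at little cost, so the change should be made, but it bears on a secondary, preliminary aim.

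**What to change.** In section 2.10, replace the MANOVA for interval-scale scores with a likelihood-based linear mixed model for each score, or for a composite:
- Include every randomised participant with at least one assessment, and all available visits. State that no one is dropped because another test or a later visit is missing.
- Fit a participant random effect and fixed effects for period/visit, sequence (group) and the condition received (CEREBRUM or usual care). A visit-by-group model alone would ignore that group B crosses to CEREBRUM.
- Base the CEREBRUM versus usual-care contrast on assessments where the two groups are under different conditions, and name those assessments. Report the 6- and 12-month follow-ups descriptively, because both groups have received CEREBRUM by then.
- Keep the MANOVA, if wanted, as a sensitivity analysis with its row layout stated.

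The cost is wording and a modest amount of extra analysis, with no new visits or participants. The omnibus test gives way to several models, whose results should be labelled exploratory. Validity then rests on missingness being at random given the observed scores.

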### Study Design

2.1

This is a randomized, controlled cross-over clinical feasibility study. This study follows the CONSORT flow diagram extension for feasibility study [34]. The protocol has been written according to the Standard Protocol Items (SPIRIT checklist) [35].

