### Randomization

2.3

Eligible participants were randomized into two groups, using a computer-generated randomization list. The biometrician responsible for the randomization process was blinded to the identities of participants. The experimental group (A) receives the CR intervention with virtual reality (CEREBRUM) lasting 3 months (two weekly meetings) and the control group (B) receives treatment as usual. When group A receives the “CEREBRUM” intervention, group B receives treatment, as usual, 1 month after the end of the intervention for group A (washout period) group B receives the “CEREBRUM intervention becoming experimental group and group A the routine intervention (Table **1**).

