### Sample Size Considerations

2.11

To date there is still poor evidence in this field of research for establishing an effective methodology in terms of sample size, and in this sense, the aim of this study is to verify the feasibility [20, 59]. We randomized 50 participants in order to be able to assess the feasibility outcomes: recruitment and retention rates Fig. (**1**).

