## CONCLUSION

Mental health is a fundamental resource that allows people to achieve daily goals in life and exercise the role of a citizen of a community. Bipolar disorder is recurrent condition that severely impacts the lives of people living with the experience; it is considered one of the leading causes of disabilities in the world [3]. To date, there is a lack of evidence for the treatment of cognitive deficits in BD even if cognitive deficits are a core component of personal and social functioning. The principle neuropsychological deficits are in attentional capacities, executive functions, and episodic/verbal memory [9]. The application of innovation science is increasing in the mental health field and the use of technologies can have a positive impact on psychiatric rehabilitation. The crossover study is a clinical study in which each group consecutively receives the treatments subjected to the study. This guarantees as an advantage a low variance given that the treatment and control correspond to the same participant (allows precise comparisons between multiple treatments) and it also guarantees the provision of the clinical intervention to all participants. The results of this study might have an impact on future studies, in particular, in the field of psychosocial intervention for the treatment of cognitive dysfunction in bipolar disorder and also in the technological innovation field for mental health rehabilitation.

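### The effectiveness MANOVA is described by time-by-group sub-samples with no participant, period or sequence term, although the cross-over is justified by within-participant comparison

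*Protocol article*

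**What the plan says.** All references are to the protocol article.

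- **Design (2.1):** "This is a randomized, controlled cross-over clinical feasibility study".
- **Switch of condition (2.3):** after the washout, "group B receives the “CEREBRUM intervention becoming experimental group and group A the routine intervention". Each person is therefore scheduled to supply data under both conditions.
- **Assessments (2.8):** "Participants were assessed before the treatment, after the end of the intervention, and after 6 and 12 months after the end of the intervention", which makes four occasions.
- **Reason for the design (Conclusion):** "This guarantees as an advantage a low variance given that the treatment and control correspond to the same participant".
- **Analysis (2.10):** "The outcome of the trial was analyzed through multivariate analysis of variance (MANOVA"), with mean scores that "were compared in sub-samples divided by the two independent variables [time and group (intervention and non-intervention".
- **Fallback (2.10):** "For variables not on an interval scale, the analysis of variance for nominal data by De Castellan was used with a similar methodology".
- **Sample size (2.11):** "We randomized 50 participants in order to be able to assess the feasibility outcomes: recruitment and retention rates". No alpha, power, effect size, standard deviation or correlation is given.

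**The concern.** The design sections and the analysis section do not fit together. A cross-over gains precision only if the analysis compares each person with himself or herself and separates treatment from period and order. Section 2.10 names two factors, time and group. It defines group as intervention versus non-intervention, but every participant is due to be in both states, and the text does not say how such a person is classified. No term carries the pairing, the period or the sequence.

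If the paragraph is followed literally, the p-values and confidence intervals for the effectiveness outcomes would be wrong by an amount that depends on the within-person correlation, and the precision claimed in the Conclusion would be lost. Preliminary clinical effectiveness is a stated secondary objective (1.1.2), so these results will be read.

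The fallback rule has a separate weakness. Variables that are not on an interval scale include ordinal ratings as well as nominal categories, and a method for nominal data takes no account of order.

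**Working it through.** The plan has no figure to reproduce on this point, so the check asks what a plain factorial analysis of person-visits would do.

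**Inputs from the protocol article:** 50 participants (2.11), two groups (2.3), four assessments (2.8).

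**Assumptions, not in the document:** 25 per group, no dropout, two-sided alpha 0.05, equal correlation rho between any two visits of one person (shown at 0.5 and 0.7).

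**Within-person contrast.** The difference between two visits has true variance 2σ²(1−rho). Treating the visits as unrelated gives 2σ². The standard error is overstated by 1/√(1−rho):
- rho 0.5: 1/√0.5 = 1.41
- rho 0.7: 1/√0.3 = 1.83

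The true size of a nominal 5% test is 2[1−Φ(1.96 × ratio)], which gives 0.6% and 0.03%.

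**Between-person contrast averaged over T visits.** A person's mean has true variance σ²[1+(T−1)rho]/T. The naive variance is σ²/T. The ratio of naive to true standard error is 1/√[1+(T−1)rho]:

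| T | rho | ratio | true size of a 5% test |
|---|---|---|---|
| 2 | 0.5 | 1/√1.5 = 0.82 | 11.0% |
| 2 | 0.7 | 1/√1.7 = 0.77 | 13.3% |
| 4 | 0.5 | 1/√2.5 = 0.63 | 21.5% |
| 4 | 0.7 | 1/√3.1 = 0.57 | 26.6% |

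**Which error appears depends on what group and time mean.** Three readings were simulated (4,000 trials each, no true effect, rho 0.5, Wilks test; one dependent variable / three with correlation 0.4):
1. Group is the randomised arm, four visits: the group effect rejects in 22% / 36%; time and interaction in at most 0.3%.
2. Group is the condition, time is the period: condition and period reject in at most 0.6%; their interaction, which is the sequence contrast, in 11% / 17%.
3. Group is the condition, time is before and after within each period: all three effects reject in at most 0.8%.

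Readings 1 and 2 give errors in both directions. Reading 3, in which every person is in every cell, gives only standard errors that are too large.

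**Cost in power for the cross-over contrast.** Take 50 people over two periods and an assumed effect of 0.5 SD. The true standard error is √[2(1−rho)/50] and the naive one is √(2/50) = 0.20.
- rho 0.5: true standard error 0.141; power 78% ignoring pairing, 94% with it.
- rho 0.7: true standard error 0.110; power 84% ignoring pairing, 99.5% with it.

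**Nominal fallback, illustration only.** Suppose a five-level ordinal outcome whose difference lies along the order. A 1-df ordered test with 80% power has non-centrality 7.85. The same signal on 4 df has power 59.5%. Section 2.10 does not list which variables go to the fallback.

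**The case against.** The strongest reply is that Section 2.10 never says observations are treated as statistically independent. Independent variables there means explanatory factors. A repeated-measures MANOVA also has time and group as its factors and is not excluded by the wording. The paragraph is an article's summary, and the error structure could be set out in a fuller plan. This stands, and it limits the point: the numerical errors above are conditional on a plain factorial analysis.

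Several stronger readings are tempting and are not supported:

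- **That the standard errors are wrong in both directions because the same people supply every cell.** The two halves do not hold together. If everyone is in every cell, all contrasts are within-person and the error is one-directional. The anti-conservative error needs an arm or sequence contrast, where each person fills only some cells.
- **That practice effects must contaminate the treatment contrast.** In an arm-by-visit analysis, changes common to both arms cancel in the interaction. Section 2.8 also provides alternate test versions where learning is a concern.
- **That unreliable effect sizes and standard deviations would pass to the confirmatory trial.** The Discussion names recruitment and retention rates as what informs its sample size. Ignoring pairing distorts standard errors and tests, not cell means or cell standard deviations.
- **That a repeated-measures MANOVA would fail for lack of complete cases.** This assumes that all cognitive scores enter one model, which the article does not say.

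What survives is the mismatch itself. The article does commit to a procedure, two factors and a fallback method. As stated, these do not carry the feature for which the design was chosen.

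**Conclusion.** The point holds as a mismatch between design and stated analysis. Section 2.10 describes time-by-group sub-samples without a participant, period or sequence term, in a trial whose Conclusion rests on within-participant comparison. A plain factorial analysis would give wrong standard errors under each of the three readings examined; their direction depends on how group and time are defined, and their size on a correlation that the article does not give. That the trial will in fact be analysed this way is an inference that the text permits but does not establish. The loss of order under the nominal fallback follows from the sentence itself for any ordinal rating sent there; its size is not known.

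Severity is moderate. The MANOVA concerns test scores, which are secondary and preliminary. The co-primary recruitment and completion proportions (2.7) and the reason given for 50 participants (2.11) are unaffected.

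**What to change.** For the secondary effectiveness outcomes, replace the MANOVA in Section 2.10 with a linear mixed model for each outcome, using all available data and a participant random effect.

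- **When both periods are used:** fixed effects for treatment condition, period and sequence.
- **When only the first period is compared:** fixed effects for randomised group, visit and group-by-visit, with the baseline score as covariate.
- **Reporting:** estimates with 95% confidence intervals.
- **Ordinal outcomes:** a proportional-odds mixed model in place of the nominal-data method.

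If a within-participant analysis was intended all along, the minimum is to say so, to define group for a person who receives both conditions, and to state how period and sequence are handled. A repeated-measures MANOVA or a standard two-period cross-over analysis would also resolve the mismatch; the mixed model is preferred because it keeps participants with incomplete scores.

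The cost is analysis wording and a little more programming. No extra participants or visits are needed.

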### Participant Identification

2.2

The participants with psycho-social disabilities were recruited at the Consultation and Psychosomatic Psychiatry Center of the University Hospital of Cagliari (San Giovanni di Dio Civil Hospital).

*Inclusion Criteria:* age from 18 to 75; diagnosis of bipolar disorder according to DSM-IV [36]; both sexes; users who sign the informed consent; users under protection for which the informed consent is signed by the support legal administration.

*Exclusion Criteria:* The non-satisfaction with the inclusion criteria; *the presence of maniac/depressive phases;* the diagnosis of epilepsy or serious eye diseases, due to the risk associated with the excessive stimulation of virtual reality.

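### Section 2.10 enters the pre-treatment test score at most as a level of time; using it as a covariate in the first-period comparison would be more precise at almost no cost

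*Protocol article*

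**What the plan says.** Section 2.10 (Data Analysis) of the protocol article names the method: "The outcome of the trial was analyzed through multivariate analysis of variance (MANOVA"). The dependent variables are the performance-test scores, whose means "were compared in sub-samples divided by the two independent variables [time and group (intervention and non-intervention"). No covariate is named. The section does not say whether the CEREBRUM effect is the group main effect or the group-by-time interaction.

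The information for an adjusted analysis is already collected:

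- Section 2.8 (Data collection): "Participants were assessed before the treatment, after the end of the intervention, and after 6 and 12 months after the end of the intervention". The pre-treatment score is therefore available and is one of the time points.
- Section 2.9 (Sample Variables) records "Gender and age; Marital status; Educational qualification".
- Section 2.2 (Participant Identification) admits "age from 18 to 75".

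Section 2.3 (Randomization) describes a computer-generated list and names no stratification factor. In the cross-over, group B receives CEREBRUM after a one-month washout. Section 2.11 gives 50 randomised participants.

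**The concern.** A person's own pre-treatment score on a cognitive test is usually the best available predictor of that person's later score. A two-factor comparison of means can use it in only two ways. It can ignore the baseline, by reading end scores, or average it in, through a group main effect; a chance gap at entry then carries into the estimate. Or it can subtract the baseline in full, through the group-by-time contrast; this over-corrects whenever the correlation between baseline and outcome is below 1. A covariate model removes only the part of the gap that predicts the outcome, and has the smaller variance.

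At stake are the accuracy and interval width of the preliminary effectiveness estimates, which section 1.1.2 lists as a secondary objective. In a trial of this size chance gaps are common, and nothing in section 2.3 limits them.

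**Working it through.** The article states no power, effect size, SD or correlation for the test scores, so there is no figure to reproduce.

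**Inputs.** From the article: 50 randomised (section 2.11), two groups (section 2.3), and a pre-treatment and end-of-intervention score (section 2.8). Assumed: 25 per group, equal SD of 1 at both times, true effect 0.5 SD, two-sided alpha 0.05, baseline-to-outcome correlation r from 0.3 to 0.9. The comparison is that of the first period.

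**Step 1: chance imbalance.** The SD of the baseline mean difference is sqrt(2/25) = 0.283 SD, and its 95% range is ±1.96 × 0.283 = ±0.55 SD. A gap above 0.3 SD in either direction has probability 2 × [1 − Φ(0.3/0.283)] = about 29%.

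**Step 2: what a +0.3 SD gap does to the estimate.** The expected error is r × 0.3 for end scores, (r − 1) × 0.3 for the change contrast, and about 0 with the baseline as covariate.

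| r | End scores | Change contrast | Baseline-adjusted |
|---|---|---|---|
| 0.5 | +0.15 | −0.15 | 0 |
| 0.7 | +0.21 | −0.09 | 0 |
| 0.8 | +0.24 | −0.06 | 0 |

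**Step 3: variance.** In units of 2·SD²/n the variance is 1 for end scores, 2(1 − r) for change and 1 − r² for baseline-adjusted. The ratio of adjusted to change is (1 − r²)/[2(1 − r)] = (1 + r)/2. This gives 0.65 at r = 0.3, 0.75 at 0.5, 0.85 at 0.7, 0.90 at 0.8 and 0.95 at 0.9.

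**Step 4: power.** SE = sqrt(2v/25), where v is the variance from step 3. Power is from the noncentral t with 48 degrees of freedom, or 47 with the covariate.

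| r | Change: SE, power | Adjusted: SE, power |
|---|---|---|
| 0.5 | 0.283, 41% | 0.245, 52% |
| 0.7 | 0.219, 61% | 0.202, 68% |
| 0.8 | 0.179, 78% | 0.170, 82% |

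An end-score comparison has SE 0.283 and power 41% whatever r is.

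**Step 5: simulation check.** There were 20,000 first-period trials per value of r, with age and education assumed to explain 30% of score variance. At r = 0.5, 0.7 and 0.8 the baseline-adjusted variance was 0.77, 0.52 and 0.37. The formula gives 0.75, 0.51 and 0.36; the small excess is the price of estimating the slope. Adding age and education lowered it to 0.68, 0.49 and 0.35. The slope of the estimate on an age/education imbalance was about 0.55 for end scores or the group main effect, and about 0.00 for the group-by-time contrast.

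**The case against.** Four objections carry weight.

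1. **The baseline is not left out.** Time is a factor and the pre-treatment assessment is one of its levels. A reader might infer that imbalance in age and education stays in the CEREBRUM estimate. Under the group-by-time reading it does not: stable age and education effects cancel, as step 5 shows. It stays only if end scores or a group main effect are read, which section 2.10 neither states nor excludes.
2. **The large gain uses an unfavourable comparator.** A reader might set 41% (end scores) against 68% (adjusted, r = 0.7) and speak of doubling the effective sample size, 1/(1 − 0.7²) = 1.96. Since time is in the model, the fair comparator is the change contrast, where the ratio is 2/(1 + 0.7) = 1.18.
3. **The design is a cross-over.** The Conclusion justifies it by comparing treatment and control within the same person, which also removes stable differences. Section 2.10, however, describes sub-samples by time and group and names no such within-person comparison.
4. **This is a condensed article about a feasibility trial.** Covariate lists are often left to an analysis plan, and effectiveness is secondary. But section 2.10 does fix the independent variables at two, so a covariate would change the stated model rather than fill in a detail.

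The first two objections set the size of the point. None of the four removes it: under either reading of section 2.10, the stated comparison is less precise than baseline adjustment over the correlations considered here.

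**Conclusion.** The point holds as a modest gain in efficiency and in robustness to chance imbalance. Over r = 0.5 to 0.8, baseline adjustment has 75% to 90% of the variance of the group-by-time contrast and adds roughly 4 to 11 percentage points of power at 0.5 SD. The gain at r = 0.7 or 0.8 is larger only if end scores alone are compared. These figures rest on the assumed 25 per group, effect size, equal SDs and correlation, none of which the article states. The advantage shrinks towards nothing as r approaches 1.

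Two stronger inferences are not supported. The planned estimate is not biased on average, because randomisation protects it; the issue is the error in a given trial and the lost precision. Nor are the primary conclusions affected: the recruitment and completion proportions in section 2.7 do not depend on this model, and section 4 ties future sample size calculations to recruitment and retention rates.

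**What to change.** In section 2.10, define the first-period contrast as group A after CEREBRUM against group B after treatment as usual, before B crosses over. For that contrast, model each test score on randomised group with the same test's pre-treatment score as a covariate, and report the adjusted mean difference with its 95% confidence interval. The restriction to the first period is essential: both groups eventually receive CEREBRUM, so a model on randomised group at the end of each group's own intervention would compare sequences rather than treatments.

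Age and education may be added as covariates for a smaller further gain, provided the list is fixed before the data are analysed. Any analysis that uses second-period data should treat time as repeated within participant.

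Cost: one degree of freedom for the baseline, a few more if age and education are added (education may need several categories), and slightly more analysis work. No new data are needed. Label: free improvement.
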